## Background

In comatose patients resuscitated from out-of-hospital cardiac arrest (OHCA), anoxic brain injuries remain the leading cause of death [1]. The overall mortality, though improved considerably over the last decade, continues to be significant and in most countries is as high as 90% [2, 3]. Despite successful resuscitation and admission to an intensive care unit (ICU), the in-hospital mortality is reported to be 30–50% [4, 5]. Functional favorable outcomes among OHCA survivors remain low, and global anoxic brain injury represents a major mechanism of long-term disability [6, 7]. During the post-resuscitative phase, the most significant clinical challenge is to limit secondary brain injury. Targeted temperature management (TTM) targeting 33–36 °C may mitigate cerebral ischemia–reperfusion injury and is recommended in current international guidelines [8–10]. However, managing post-cardiac arrest patients is far more complex than TTM alone, and brain-directed therapies include maintenance of normal oxygenation, ventilation, hemodynamic support to optimize cerebral perfusion, and glycemic control [10, 11].

Reduced cerebral blood flow (CBF), which is mainly dependent upon mean arterial blood pressure (MAP), can result in brain ischemia and enhance secondary brain injury after cardiac arrest. Arterial hypotension may exacerbate brain injury following cardiac arrest because of ongoing cerebral hypoperfusion. Cerebral autoregulation is frequently impaired after cardiac arrest [12, 13], and brain perfusion declines when the MAP falls below 80 to 100 mm Hg. Thus, the generally recommended MAP of above 65 mm Hg [11] to reverse the acute shock state may be inadequate to maintain adequate cerebral perfusion.

When considering blood pressure goals, clinicians should balance the metabolic needs of an ischemic brain with the potential for overstressing a decompensated heart. Post-cardiac arrest myocardial dysfunction, caused by coronary infarction and ischemia–reperfusion injury, is common after CA and resuscitation. Excessive vasopressor use may cause increased afterload and augmented oxygen consumption of the heart, thereby aggravating the myocardial damage [14]. High-dose vasopressor use has been associated with increased mortality [15].

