#### Phase 4 (end of intervention period to hospital discharge)

This starts when invasive blood pressure measurement is discontinued during the ICU stay.

Neurological outcome will be assessed at hospital discharge in accordance with the CPC scale [31, 32]: CPC 1, no neurological deficit; CPC 2, mild to moderate dysfunction; CPC 3, severe dysfunction; CPC 4, coma; and CPC 5, death. CPC scores of 1 and 2 are mostly considered “good” outcomes, and a CPC 3–4 “poor” outcomes. Physicians performing the CPC assessment will be blinded to patient’s LP ratio levels.

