### End-points

The study focuses on the following end-points:

Primary end-pointComparing mean LP ratio differences within 48 h between blood pressure groups and comparing individual LP ratio measurements using longitudinal analysis.

Secondary end-pointsAssociation between LP ratio and all-cause mortality during ICU stay adjusted for blood pressure groupsBetween-group difference in total duration (minutes) of cerebral desaturation defined as an absolute rSO_2_ of not more than 50% during ICU stayBetween-group difference within 48 h in lactate, pyruvate, glutamate, glycerol, and glucose measured in jugular bulbAssociation between LP ratio and cardiac index adjusted for blood pressure groupsAssociation between LP ratio and survival to hospital discharge with poor neurological function (CPC 3–4) adjusted for blood pressure groups.

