### Statistical analysis plan

The statistical analyses will be the following:Analyses will be performed in accordance with the intention-to-treat principle and will take into account patients lost to follow-up.A two-sided significance level of 0.05 will be applied to both primary and secondary end-points.Unpaired *t* tests or Mann–Whitney *U* tests will be conducted for unpaired comparisons of numerical variables. A chi-squared or Fisher’s exact test will be conducted to examine differences between categorical variables.Association between LP ratio and “poor” neurological outcome (CPC 3–4) will be assessed with chi-squared test and logistic regression. The overall expected rates of unfavorable neurological outcome (CPC 3–4) are 5–7%, observed in earlier studies [34, 35]. The multivariate logistic model will be adjusted for time to ROSC, arterial carbon dioxide partial pressure, baseline LP, and average LP ratio > 30 > 24 and 48 h as covariates.Association between LP ratio and all-cause mortality will be assessed with chi-squared test and logistic regression.Receiver operating characteristic (ROC) curves will be constructed to determine the sensitivity and specificity of the LP ratio levels at each time point (and the maximal LP ratio level recorded during the ICU period) for predicting outcomes.Association between total duration (in minutes) of cerebral desaturation (rSO_2_ ≤ 50%) and unfavorable neurological outcome (CPC 3–4) and death will be assessed with chi-squared test and logistic regression.Time from start of randomization to death in the two blood pressure groups will be assessed by using the Kaplan–Meier method, and group differences will be tested by log-rank test. Cox regression will be applied for adjusted comparisons and estimation of hazard ratios.In regard to dynamic changes of MD variables in the two blood pressure groups, longitudinal models, applying linear mixed effects regression, will be used to account for repeated measurements of MD biomarkers across different patients over time.In regard to dynamic changes of blood pressure, longitudinal models, applying linear mixed effects regression, will be used to account for repeated measurements of blood pressure across different patients over time.

All standard assumptions regarding statistical models will be checked. Statistical analysis will be performed by using STATA V.15 (StataCorp LLC).

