## Surrogate end-point

The end-point defined as the LP ratio during ICU stay is a surrogate marker for poor neurological outcome and death. The surrogate marker is used as an alternative to a hard end-point in order to power this study adequately. Previously, LP ratio studies have been shown to be a reliable marker for poor outcome after traumatic brain injury [22–26]. Hence, our surrogate end-point reflects the clinically relevant question of whether higher MAP has a potential neuroprotective effect in our population.

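### The LP ratio–neurological outcome analysis counts only CPC 3–4 as poor and puts deaths in neither class, leaving 3–4 expected events beside 18–30 deaths

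*Protocol article*

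**What the plan says.** The relevant statements stand in five sections of the protocol article.

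- **Phase 4** gives the full scale, ending "CPC 4, coma; and CPC 5, death". It then calls CPC 1–2 good "and a CPC 3–4 “poor” outcomes". Death falls in neither class.
- **End-points** lists, among the secondary end-points, the association of the LP ratio with "survival to hospital discharge with poor neurological function (CPC 3–4) adjusted for blood pressure groups". A separate secondary end-point relates the LP ratio to all-cause mortality, limited to the ICU stay.
- **Statistical analysis plan**: "Association between LP ratio and “poor” neurological outcome (CPC 3–4) will be assessed with chi-squared test and logistic regression". It adds: "The overall expected rates of unfavorable neurological outcome (CPC 3–4) are 5–7%, observed in earlier studies". The logistic model carries time to ROSC, arterial carbon dioxide pressure, baseline LP, and LP above 30 averaged over 24 h and over 48 h. The same section also plans LP versus mortality by chi-squared and logistic regression, and time to death by blood pressure group. Its desaturation analysis names death alongside CPC 3–4.
- **Background**: "the in-hospital mortality is reported to be 30–50" per cent. Anoxic brain injury is named there as the leading cause of death.
- **Surrogate end-point**: the LP ratio "is a surrogate marker for poor neurological outcome and death".

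**The concern.** Aim (c) is to relate the LP ratio to neurological outcome on the CPC scale. In this population most bad outcomes are deaths, so the handling of CPC 5 largely determines what the analysis measures. The article fixes the event but not the comparison group, and both possible readings cause trouble.

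- **Deaths as non-events.** Patients who died are pooled with those who recovered well. If they had high LP ratios, the comparison group's LP ratio rises and the contrast shrinks.
- **Deaths left out.** The analysis is restricted to survivors, although survival is itself something the LP ratio is expected to predict. Very few events then have to support a multivariable model.

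The word overall, attached to the 5–7% rate, suggests an all-patient denominator and hence the first reading, but the article does not say so. What is at stake is a null or uninterpretable answer to aim (c), even if the LP ratio is a good marker of brain injury.

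**Working it through.** **Inputs from the article.** N = 60 and SD of LP = 15 (Sample size estimation); CPC 3–4 rate 5–7% (Statistical analysis plan); in-hospital mortality 30–50% (Background).

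**1. The plan's own sample size.** The only stated figure is 46 patients, for the primary end-point. With a difference of 35 − 20 = 15 and SD 15, n per arm = 2 × (1.96 + 1.2816)² × (15/15)² = 21.01, rounded up to 22 (44 in total). The t-based solution is 22.02, rounded up to 23, which gives 46. The figure is reproduced, and nothing below touches it. No sample size is stated for the CPC end-point.

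**2. Expected counts at N = 60.**
- Deaths: 60 × 0.30 to 60 × 0.50 = 18 to 30.
- CPC 3–4: 60 × 0.05 to 60 × 0.07 = 3.0 to 4.2.
- Share of deaths among non-events: 0.30/0.95 = 32% to 0.50/0.93 = 54%.
- Survivors if deaths are left out: 42 to 30. If the 5–7% applied to survivors only, events would be 30 × 0.05 = 1.5 to 42 × 0.07 = 2.9.
- CPC 3–5: 60 × (0.30 + 0.05) = 21 to 60 × (0.50 + 0.07) = 34.2.

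**3. Events per model term.** The five listed covariates plus blood pressure group make six terms. CPC 3–4 gives 3.0/6 = 0.5 to 4.2/6 = 0.7 events per term. CPC 3–5 gives 21/6 = 3.5 to 34.2/6 = 5.7, which is still thin.

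**4. Effect of counting deaths as non-events.** Assume LP is normal with SD 15 in each outcome class, a mean of 20 in CPC 1–2, and a CPC 3–4 rate of 6%. The class means are assumptions. P(LP > 30) = 1 − Φ((30 − mean)/15), which is 0.2525 at mean 20, 0.5 at mean 30 and 0.6306 at mean 35.

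Worked case, with means 30 (CPC 3–4) and 35 (deaths):
- CPC 3–4 versus 1–2: odds 1 against 0.2525/0.7475 = 0.3378, so OR = 2.96.
- Deaths as non-events, 30% mortality: P = (0.64 × 0.2525 + 0.30 × 0.6306)/0.94 = 0.373, odds 0.595, OR = 1/0.595 = 1.68.
- Deaths as non-events, 50% mortality: P = (0.44 × 0.2525 + 0.50 × 0.6306)/0.94 = 0.454, odds 0.830, OR = 1.20.

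The same calculation for other assumed means (ORs for LP > 30, at 30% / 50% mortality):

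| Mean CPC 3–4 | Mean deaths | Deaths left out | Deaths as non-events | CPC 3–5 vs 1–2 |
|---|---|---|---|---|
| 30 | 20 | 2.96 | 2.96 / 2.96 | 1.23 / 1.15 |
| 30 | 30 | 2.96 | 2.02 / 1.60 | 2.96 / 2.96 |
| 30 | 35 | 2.96 | 1.68 / 1.20 | 4.61 / 4.76 |
| 30 | 40 | 2.96 | 1.44 / 0.94 | 7.12 / 7.65 |
| 25 | 35 | 1.73 | 0.98 / 0.71 | 4.21 / 4.49 |
| 35 | 35 | 5.05 | 2.87 / 2.06 | 5.05 / 5.05 |

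There is no attenuation if deaths have the same LP as CPC 1–2. Attenuation appears in every row where deaths have a higher LP. The OR falls below 1 only where the mean LP in deaths is above that in CPC 3–4 survivors, and not in all such rows.

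**5. A second model.** Assume one ordered outcome with an OR of 2.7 per SD of LP (an assumption), 6% CPC 3–4, and mortality of 30/40/50%. CPC 3–4 versus all others gives an OR of about 1.3/1.1/0.96, and survivors only about 1.95/1.8/1.7. CPC 3–5 returns 2.7, which it must by construction. If half of the deaths are unrelated to LP (also an assumption), the figures are about 1.6/1.4/1.2 for deaths as non-events, 2.17/2.04/1.92 in survivors, and about 1.9 for CPC 3–5.

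**The case against.** The strongest defence is that the end-point is openly worded as survival with poor function, that its low rate is disclosed, and that death has its own place in the plan. LP versus mortality is a separate secondary end-point, and in the ordered model of step 5 that analysis recovers the full OR of 2.7. A reader might infer that the plan ignores deaths, and it does not. A reader might also extend the fault to the desaturation analysis, but that analysis already names death.

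This narrows the point without removing it. The separate mortality end-point covers the ICU stay only, so a death after ICU but before discharge is an event in neither LP end-point as listed. The Kaplan–Meier and Cox analyses compare blood pressure groups, not LP levels. Nor is this a detail that an article may leave to a fuller document: the event is defined here, on a scale whose last category is left unassigned.

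The second objection is that CPC 3–5 is a trade-off. That is partly right. If half of the deaths are unrelated to LP, the composite OR falls from 2.7 to about 1.9, and the survivors-only OR is as large or larger. But the composite still exceeds the deaths-as-non-events figures (about 1.6/1.4/1.2), and it rests on 21–34 events, not on 3–4 in a group selected by survival. If deaths were wholly unrelated to LP, the composite would do worse (first row of the table), but that contradicts the article's own premise.

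**Conclusion.** The point holds for the secondary LP–CPC analysis and for any ROC curve that uses the same CPC 3–4 outcome. On the article's own rates, 3–4 events stand beside 18–30 deaths that have no assigned class. As non-events, the deaths would make up 32–54% of the comparison group and would probably attenuate the association. That conclusion rests on the LP ratio being higher in patients who die, which is the article's premise and not an established fact. With deaths left out, the difficulties are survivor selection and about 0.5–0.7 events per term, not necessarily attenuation.

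A reader might infer that the association would be reversed, so that a high LP ratio looks protective. The documents do not support this. Reversal needs deaths to have clearly higher LP than CPC 3–4 survivors, on which the article gives no figures. In the ordered model the only value below 1 is about 0.96, at 50% mortality, which is essentially null. Nor does the point reach the primary end-point, the sample size or the randomised comparison. It should be fixed, but it does not threaten the trial's main result.

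**What to change.** Define poor neurological outcome as CPC 3–5 versus CPC 1–2 in all randomised patients at hospital discharge. Use that definition in the LP chi-squared and logistic analyses and in any ROC curve for neurological outcome. Repeat the analysis with the 3-month CPC that Phase 5 already collects. Keep LP versus mortality as its own end-point, and report CPC 3–4 among survivors as a descriptive count.

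If the sponsor prefers to keep a survivor end-point, the text should state that deaths are excluded and that the result applies to survivors only, and the multivariable model should be dropped for it.

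The cost is a change of wording in Phase 4, End-points and Statistical analysis plan, made before the outcome data are analysed. No new data are needed. The downside is that the composite takes in deaths of non-neurological cause, which dilutes the association. Deaths should therefore be reported by presumed cause alongside it. Phase 3 already plans this for deaths before neurological prognostication, and it would need extending to all deaths before discharge. With 3.5–5.7 events per term, the covariate list remains long even after the change.

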### Sample size estimation

The sample size was calculated on the basis of the primary hypothesis but taking into account only the mean LP ratio and not the individual measurements; this was due to insufficient information about interpretation variation in LP values; this implies a conservative error and hence the true power of the study is expected to be higher than in this calculation. The trial is designed as a randomized study, and we have chosen to power this study according to differences in the LP ratio. A difference of 30% between groups is defined as the minimal clinically relevant difference. Assuming an average LP ratio of less than 20 over 48 h in the high MAP group compared with more than 35 over 48 h in the low MAP group, we will need to include 46 patients in total to achieve a power of 0.9 using a patient-to-patient variation with standard deviation (SD) of 15 in LP ratio as motivated by an earlier study [29] in the power calculation and assuming normal distribution of LP ratio. To take possible higher patient-to-patient variation in this study as well as deviations from normality into account, we plan to include at least 60 patients in total. Defining an LP ratio of more than 30 averaged over 24 and 48 h for both groups, we will analyze the proportion of patients reaching that end-point in each group.

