**Fig. 1 Fig1:**
[figure not shown]
Schematic diagram of cerebral metabolism. Schematic illustration of cerebral intermediary metabolism is shown with a focus on the glycolytic pathway and its relation to glycerol, glycerophospholipids, and the citric acid cycle. *Abbreviations*: *α-KG* α-ketoglutarate, *DHAP* dihydroxyacetone-phosphate, *F-1,6-DP* fructose-1,6-diphosphate, *FFA* free fatty acid, *G-3-P* glycerol-3-phosphate, *GA-3P* glyceraldehyde-3-phosphate. Underscored metabolites are obtained at the bedside with enzymatic techniques.

Clinical MD monitors the supply of glucose and its metabolism via glycolysis to pyruvate, which under oxidative conditions enter the tricarboxylic acid cycle. During hypoxic conditions or if mitochondrial function is compromised, pyruvate is metabolized to lactate. Therefore, the LP ratio is used as a marker of aerobic versus “anaerobic” metabolism not requiring oxygen [22]. High LP ratio is considered a robust indicator of anaerobic metabolism and the redox status of the tissue and is an independent predictor of mortality and unfavorable outcome in traumatic brain injury among patients monitored with MD [23–27]. An increased LP ratio could result from a failure of oxygen delivery (ischemic hypoxia) or no ischemic causes (e.g., mitochondrial dysfunction) [28]. An increase in the LP ratio in the presence of low pyruvate (and low oxygen pressure) indicates ischemia. In contrast, an increase in LP ratio in the presence of normal or high pyruvate (and normal oxygen pressure) indicates mitochondrial dysfunction. With intracerebral MD, the normal upper limit for the LP ratio of the human brain has been defined as 30 [22, 24]. Increased levels of glutamate and glycerol indicate hypoxia/ischemia and have been defined as indicators of excitotoxicity and cell membrane breakdown, respectively [19].

The LP ratio obtained from MD of cerebral venous blood may be a sensitive indicator of impending cerebral damage and secondary neurological deterioration and might play a critical role in detecting the early responses of post-resuscitation care. The use of global cerebral MD may potentially aid clinicians in providing individualized and tailored brain resuscitation strategies that prevent secondary brain injury and lead to improved survival and neurological outcomes after cardiac arrest.

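### The LP > 30 limit comes from brain-tissue microdialysis and is applied unchanged to jugular blood; code LP as continuous in the outcome models and keep the proportion above 30 as descriptive

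*Protocol article*

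**What the plan says.** The Background (text following Fig. 1) is the only place that says where the limit comes from: "With intracerebral MD, the normal upper limit for the LP ratio of the human brain has been defined as 30". The section on bedside monitoring places the trial's catheter in the jugular bulb, where it samples venous blood.

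The limit is then used twice.

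- **Sample size estimation**, last sentence: "Defining an LP ratio of more than 30 averaged over 24 and 48 h for both groups, we will analyze the proportion of patients" above that value in each arm. This proportion does not appear in the End-points section.
- **Statistical analysis plan**, multivariable logistic model for CPC 3–4: besides time to ROSC, carbon dioxide pressure and baseline LP, the model lists "average LP ratio > 30 > 24 and 48 h as covariates". No other post-baseline LP term is listed.

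The association of LP with all-cause mortality is to be assessed by a chi-squared test and logistic regression. The coding of LP is not stated there, but a chi-squared test implies some categorisation.

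The End-points section makes the primary comparison the mean LP ratio over 48 h, with a longitudinal analysis of the individual values.

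**The concern.** A limit that marks abnormal values in brain tissue need not mark them in venous blood. The article says that jugular monitoring represents overall cerebral metabolism. That is a statement about tracking and does not show that the two media share a numerical upper limit. The section on strengths and limitations adds that no gold standard exists for comparison, so the article offers no calibration. A reader of the results could take a jugular LP above 30 as established metabolic derangement, which the article does not show.

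The second issue is separate and general. LP is measured hourly on a continuous scale, and reducing its average to above or below 30 discards information in the analyses that use the split. What is at stake is the supplementary proportion and the association of LP with poor neurological outcome, which is a listed secondary end-point. If mortality is also analysed on categorised LP, that association is affected too.

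**Working it through.** **Inputs, all from the protocol article**

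- Means: "Assuming an average LP ratio of less than 20 over 48 h in the high MAP group compared with more than 35" in the low MAP group; taken as 20 and 35, difference 15.
- Spread: "using a patient-to-patient variation with standard deviation (SD) of 15 in LP ratio", normal distribution.
- Test level: "A two-sided significance level of 0.05 will be applied to both primary and secondary end-points".
- Size: at least 60 in total, allocated one to one, so 30 per arm.

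**Step 1: reproduce the plan's own figure.** The article states "we will need to include 46 patients in total to achieve a power of 0.9". The standardised difference is 15/15 = 1. A two-sample t test at two-sided 0.05 and power 0.90 needs 22.02 per arm, rounded up to 23, so 46 in total. The figure reproduces exactly.

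**Step 2: power of the continuous mean at 30 per arm.** The same t test gives 0.968.

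**Step 3: proportions above 30 under the same assumptions.**

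- Low MAP: 1 − Φ((30 − 35)/15) = 1 − Φ(−0.333) = 0.631
- High MAP: 1 − Φ((30 − 20)/15) = 1 − Φ(0.667) = 0.252

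**Step 4: power of the split, by exact binomial enumeration at 30 v 30.** To separate the cost of splitting from the cost of using 30 in particular, the midpoint of the two means, (20 + 35)/2 = 27.5, is included as the best cut.

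| Analysis of LP | Low v high MAP | Power, chi-squared | Power, Fisher |
|---|---|---|---|
| Continuous mean (t test) | 35 v 20 | 0.968 | – |
| Cut at 27.5 | 69.1% v 30.9% | 0.867 | 0.800 |
| Cut at 30 | 63.1% v 25.2% | 0.860 | 0.791 |

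Splitting at the best cut costs 0.968 − 0.867 = 0.101 (chi-squared) or 0.968 − 0.800 = 0.168 (Fisher). Moving from 27.5 to 30 costs a further 0.867 − 0.860 = 0.007, or 0.800 − 0.791 = 0.009. Both are under one percentage point.

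**Step 5: sensitivity.**

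- The article says "A difference of 30% between groups is defined as the minimal clinically relevant difference". Read as 30% off the low MAP mean, this is 35 × 0.7 = 24.5, so 35 v 24.5 with SD 15. Power is 0.760 continuous, against 0.580 (chi-squared) or 0.474 (Fisher) for LP > 30.
- With an SD of 20, an assumed value for the higher variation the article anticipates, power is 0.815 against 0.633 or 0.529.

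The loss from splitting is larger in both cases.

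**Step 6: LP as a model term.** With both arms pooled under the planning inputs, the squared correlation between mean LP and the LP > 30 indicator is 0.64. If outcome varies linearly with LP, the indicator carries roughly two thirds of the information.

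**Step 7: events for the CPC 3–4 model.** The article expects 5–7%: 60 × 0.05 = 3.0 and 60 × 0.07 = 4.2, so about 3 to 4 events.

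**Step 8: misclassification, by assumption only.** If the true jugular limit lay 5 units from 30, about 11–12% of patients would fall in the wrong class under the planning distributions; at 10 units, about 21–23%. Nothing in the article indicates that such an offset exists, or its size or direction.

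**The case against.** The strongest reply is that the trial already does the important thing. The primary comparison is continuous, the sample size rests on the continuous mean, and linear mixed models use the individual values. The ROC curves assess LP levels without reference to 30. The LP > 30 proportion is one added sentence for which no power is claimed. All of this stands.

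Three stronger readings are tempting, and the article does not support them.

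- *The brain-tissue cut-off costs the trial power.* The loss comes from splitting LP at all and would occur with a validated jugular limit too. Under the planning means, 30 lies close to the best cut. Nothing the trial was sized for is affected.
- *Venous values sit on another scale, so patients will be misclassified.* The article shows no offset. Its planning means of 20 and 35 lie on either side of 30, and the planning SD is drawn from an earlier study by the same group, which the Background describes as using jugular bulb microdialysis. Whether 30 carries over is unshown, which is different from being shown wrong.
- *LP > 30 is the declared LP exposure in the outcome model.* The article names LP ratio as what is associated with outcome and lists the LP > 30 terms as adjustment covariates, in a condensed phrase. That they are the only post-baseline LP terms listed is a fact; that they are the sole exposure is an inference.

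It is also fair to say that with 3 to 4 events the CPC 3–4 model is weak however LP is coded. That limits the gain from recoding that model but does not remove the reason to do it. The gain is clearer for mortality, where the planned chi-squared test implies categorised LP.

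**Conclusion.** The point holds as a matter of coding and interpretation in supplementary and secondary analyses. The limit of 30 is stated for intracerebral microdialysis, no jugular limit is given, and the article nevertheless uses 30 for a between-arm proportion and for the only post-baseline LP terms in the CPC 3–4 model.

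For the between-arm comparison at 30 per arm, splitting at 30 lowers power from 0.97 to 0.86 (chi-squared) or 0.79 (Fisher). These figures rest on the protocol's means, SD and normality. They do not measure the loss in the outcome models, for which the article gives no effect size.

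The tissue origin matters for what a jugular value above 30 may be said to mean. The primary end-point, the sample size and the ROC analyses need no change. Severity: consider.

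**What to change.** In the Statistical analysis plan section:

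1. Replace the LP > 30 indicators in the CPC 3–4 logistic model with averaged LP as a continuous term, for example per 10 units or log-transformed.
2. Use the same coding in the mortality model, in place of a chi-squared test on categorised LP.

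In the Sample size estimation section, keep the LP > 30 proportion as a descriptive display only, labelled as an intracerebral threshold that has not been established for jugular blood. The between-arm comparison needs no other change, because the continuous analysis is already primary.

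The cost is wording: the hourly values are already collected, and no new threshold is needed. The downside is that a continuous effect is less easily quoted than a proportion. With about 3 to 4 expected CPC 3–4 events, the recoding does not by itself make that model reliable, and its report should say so.
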